**Primary objective “A”**				
Determine the proportion of primary care clinics who are approached and agree to participate	Feasibility of clinic recruitment and retention	(i) Percentage of eligible clinics who are approached and enroll; *RC tracking*	**Criteria for success** (i) A 60% or greater enrollment rate of primary care clinics approached for participation	(i) Descriptive counts, percentages, and range across provinces
**Primary objective “B”**				
Determine the proportion of primary care providers who (i) enroll in the study, (ii) complete all VEGA modules, (iii) are retained for all follow-up timepoints	Acceptability and feasibility of VEGA education Acceptability and feasibility of staff recruitment and retention procedures	(i) Percentage of eligible providers that enroll; *RC tracking* (ii) Percentage of enrolled providers that complete all VEGA modules; *RC tracking* (iii) Percentage of providers that complete quantitative research assessments at all timepoints; *RC tracking*	**Criteria for success** (i) A 60% or greater enrollment rate of providers at each of the clinics; (ii) A 70% or greater VEGA completion rate among enrolled providers; (iii) 70% or more of enrolled providers will be retained at a 12-week follow-up	(i–iv) Descriptive counts, percentage, and range across provinces
**Primary objective “C”**				
Determine the feasibility of collecting provider-level outcome data at baseline, 1-, and 3-month follow-up timepoints	Feasibility of secondary outcome data collection	Percentage of missing data on secondary outcomes at each time point; *RC tracking* Percentage of missing research assessments; *RC tracking*	**Criteria for success**: There will be less than 20% missing data at the individual and group level for each timepoint Our RC is able to generate estimates of effect and variability (with 95% confidence intervals) for the secondary outcomes	Percentages and range of missing data at the item, individual, and group level across sites for each of the secondary outcome measures and across secondary outcome measures Regression estimates and associated confidence intervals
**Primary objective “D”**				
Explore the acceptability and feasibility of the intervention and evaluation procedures in (i) a sub-sample of providers who fully completed the VEGA intervention, as well as (ii) managers of participating primary care clinics	Acceptability of training Acceptability of research procedures Proof-of-concept/clinical impact	Narrative descriptions of perceived acceptability and burden of intervention and research activities; *qualitative interviews with providers and clinic managers* Narrative description of perceived value and impacts of intervention in practice; *qualitative interviews with providers and clinic managers.* Narrative descriptions of implementation successes and challenges; *consultation sessions with providers*	**N/A**	Directed content analysis; summative content analysis; thematic analysis

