##### Quantitative data collection

Quantitative data related to acceptability and feasibility will be collected by the project’s research coordinator (RC); this will include tracking the number of clinics approached for participation, who request preparatory webinars, and who enroll. It will also involve tracking HSSPs within each clinic who (a) inquire about participation, (b) are eligible, and (c) enroll. The RC will also record the number of (d) (i) contacts needed to complete consent procedures and (ii) contacts to arrange all research assessments and the number of HSSPs that (e) complete VEGA training modules; (f) dropout following consent; (g) could not be reached for follow-up; (h) complete quantitative research assessments at each timepoint; and (i) are approached, agree, complete, and withdraw from the qualitative data collection strand.

Quantitative data regarding VEGA educational outcomes will be collected via HSSPs’ self-completion of assessments administered by email at three timepoints: 1 week before the intervention period (time 1; baseline), immediately following the completion of the intervention/intervention time period (time 2; post-intervention), and 3 months following intervention completion (or the intervention period for participants who take the full-time frame or who do not complete all of the VEGA learning modules) (time 3; 3-month follow-up). Given that this work is based within the overall emergent, multiphase, mixed method research design, we anticipate that measures capturing education outcomes will be the same as those administered in phase 2 of the RISE Project, which includes a brief assessment of socio-demographic characteristics. However, it is possible that these measures may expand or change throughout the duration of the research program. Additionally, at each timepoint, we will ask participants to report on the number of referrals made over the previous month to (i) intimate partner violence services, (ii) parenting services/interventions, (iii) child welfare services, or (vi) psychotherapy services.

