##### Quantitative data analysis

Given our primary focus on acceptability and feasibility, quantitative data for our primary objectives in phase 3 will be analyzed using descriptive statistics. In addition, based on our integration of sampling and recruitment recommendations in the literature [2, 3], we have proposed a priori thresholds for acceptability and feasibility as follows: the proportion of (a) primary care clinics and their HSSPs agreeing to participate will be 60% or greater; (b) enrolled HSSPs who complete all modules of the VEGA intervention will be 70% or greater; (c) missing data for each timepoint will be less than 20% at the HSSP and clinic levels; and (d) our team will be able to generate estimates of effect and variability for education outcome measures. Informed by the AIF and the broader implementation science literature, if more than one of these thresholds are not met, our team will consider revisions to our implementation and research procedures before proceeding to a definitive trial. Given our use of mixed methods, we expect that our qualitative data (outlined below) will be especially helpful for understanding how and why thresholds were or were not met and what can or should be augmented in the implementation and research procedures to bolster the possibility of future evaluation success. Secondary objectives will be addressed using regression analysis, with results being reported as estimates of effect (95% confidence interval) and associated *p*-values. Analyses will be exploratory, with no adjustments for multiple comparisons.

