#### Qualitative research strand

##### Design, sampling, and recruitment

The qualitative strand of phase 3 will follow the principles of qualitative description [62, 63]. Driven by eligibility and enrollment procedures for the quantitative strand of data collection, we will use criterion-based sampling to select a sub-sample of HSSPs (*n* = 5–10, per clinic) who provided quantitative data to participate in a qualitative semi-structured interview. This sub-sample of HSSPs will be asked to complete an interview at two timepoints: (a) within 1 week of intervention completion and (b) 2 weeks following their submission of the 3-month quantitative research assessment. We will invite HSSPs who represent various genders, education levels, employment tenure, and previous training in family violence to participate in this strand of data collection. We will also recruit up to three managers, directors, or administrators (i.e., “managers/management”) from each of the enrolled clinics to participate in this strand of data collection. Management interviews will begin immediately following the intervention period for enrolled HSSPs in the same clinic. Eligibility and consent of HSSPs will have been obtained during quantitative study enrollment; consent for qualitative data collection will be verbally reconfirmed by the RC prior to qualitative data collection. Eligible managers will be those who have been working in their management role at the enrolled clinic for at least 6 months and who intend on working at the same clinic for the duration of the study.

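### Phase 3 gives two different frames for the provider acceptability interviews: Table 3 admits only VEGA completers, and the sampling text admits non-completers without ensuring that any are interviewed

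*Protocol article*

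**What the plan says.** All references are to the protocol article, Phase 3.

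- **Table 3, primary objective D** defines the provider informants as "a sub-sample of providers who fully completed the VEGA intervention" and adds "managers of participating primary care clinics". Acceptability and burden are to be measured through interviews with these two groups. Consultation sessions with providers are a further source, listed against implementation successes and challenges.
- **Qualitative research strand, Design, sampling, and recruitment** takes 5 to 10 providers per clinic "who provided quantitative data to participate in a qualitative semi-structured interview". Each is interviewed twice: "within 1 week of intervention completion", and again 2 weeks after submitting the 3-month assessment. On diversity it says: "We will invite HSSPs who represent various genders, education levels, employment tenure, and previous training in family violence". Up to three managers per clinic are also interviewed.
- **Quantitative data collection** times the post-intervention assessment from either completion or the end of the intervention period. It also defines the 3-month assessment for participants "who do not complete all of the VEGA learning modules".
- **Quantitative data analysis** sets a threshold of 70% or more of enrolled providers completing all modules, and expects that the qualitative data "will be especially helpful for understanding how and why thresholds were or were not met".

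**The concern.** Acceptability is part of the primary aim of Phase 3, and Table 3 uses the completion rate as one of its measures. Choosing interviewees because they completed means selecting on an outcome that the interviews are meant to illuminate. Completers may on average be better disposed to the programme, or have more time for it, than those who stopped.

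The qualitative data also have a stated job: to show why thresholds were met or missed, and what to change before a definitive trial. If completion falls short of 70%, the most direct evidence on the cause would come from those who did not finish. A team that follows Table 3 will not interview them. A team that follows the sampling text may or may not. Two teams could thus apply the same protocol and reach different pictures of acceptability.

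**Working it through.** The plan gives no figure to reproduce. The check is a comparison of texts, followed by simple arithmetic on the plan's own counts.

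**1. Is a non-completer eligible for interview?**

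- Table 3, objective D: no, since full completion is part of the definition.
- Sampling section: yes, if the person gave quantitative data. Non-completers can, because the quantitative schedule provides for them.
- Table 1, Phase 3 qualitative question: it asks about providers in primary care and their managers, with no limit to completers.

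The same person is therefore eligible in one place and ineligible in another.

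**2. Does the sampling section make sure that non-completers are heard?**

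- First interview: timed from intervention completion, which a non-completer does not reach. The post-intervention quantitative assessment has the alternative anchor (end of the intervention period), but the interview schedule does not repeat it.
- Second interview: a non-completer who submits the 3-month assessment can reach it, but this is more than three months after the intervention period. One who does not submit it reaches neither timepoint as written.
- Diversity criteria: gender, education, tenure and previous training. Completion status is absent.

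So non-completers are permitted but not assured.

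**3. How many providers are affected under Table 3?**

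Inputs: 2 clinics in each of 3 provinces; 5 to 20 participating providers anticipated per clinic; 70% completion threshold; 5 to 10 interviewees per clinic.

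- Clinics: 2 × 3 = 6.
- Enrolled providers: 6 × 5 = 30 to 6 × 20 = 120.
- Planned provider interviewees: 6 × 5 = 30 to 6 × 10 = 60.
- Providers outside the frame = enrolled × (1 − completion rate):

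| Completion rate | 30 enrolled | 120 enrolled |
|---|---|---|
| 70% (the threshold) | 30 × 0.30 = 9 | 120 × 0.30 = 36 |
| 60% (assumed) | 30 × 0.40 = 12 | 120 × 0.40 = 48 |
| 50% (assumed) | 30 × 0.50 = 15 | 120 × 0.50 = 60 |

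The 60% and 50% rows are illustrations, not forecasts. They show that the excluded group grows as completion falls further below the threshold, which is when an explanation is most needed.

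**The case against.** A reader might infer that the strand shuts out the people who found VEGA unacceptable and that they cannot be heard. The document does not support this, for four reasons.

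- The sampling section is the operative recruitment text, and it already makes non-completers eligible. Its second interview is open to those who return the 3-month assessment. The section on qualitative and integrated analyses also starts data collection after the clinic's intervention period, an anchor that does not depend on individual completion.
- Non-completion is not the same as finding VEGA unacceptable. Workload, leave or turnover can also cause it, and completers can report burden.
- The qualitative strand is wider than the provider interviews. Managers are interviewed, and consultation sessions are recorded and analysed; the text limits neither to completers. The research coordinator also counts dropouts and providers who cannot be reached.
- Only some thresholds turn on non-completers. Interviewing them would not explain poor clinic or provider enrolment. Questions about value and impact in practice also reasonably need people who were exposed to the programme.

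These points limit the claim but do not remove it. The two frames still conflict. Managers can give only second-hand accounts of why a provider stopped, the consultation sessions focus on clinical application of the curriculum, and tracking counts give no account of acceptability or burden. The wider frame permits interviews with non-completers but does nothing to secure them.

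**Conclusion.** The point holds as an inconsistent sampling frame with a possible bias in one direction. If Table 3 is followed, no non-completer gives a first-hand account of acceptability or burden. If the sampling section is followed, such accounts are possible but left to chance. Either way, acceptability findings may lean favourable, and the strand is weaker at explaining a completion rate below 70%.

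At the threshold itself, the Table 3 frame leaves out 30% of enrolled providers, or 9 to 36 people. This rests on six clinics, the anticipated 5 to 20 participants in each, and completion of exactly 70%; the actual rate is unknown. The size of any bias cannot be computed from the document, since it depends on how far the views of non-completers differ from those of completers.

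The matter should be corrected before Phase 3 recruitment, because acceptability is a primary aim and the findings feed the decision on a definitive trial.

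**What to change.** 1. Reconcile Table 3, objective D, with the sampling section, so that enrolled providers who gave quantitative data are eligible for interview whatever their completion status.
2. Add completion status to the purposive sampling criteria, within the existing 5 to 10 interviews per clinic.
3. Time the first interview from completion or from the end of the intervention period, as the post-intervention quantitative assessment already is.
4. Keep the questions on perceived value and impact in practice for those exposed to VEGA, and ask every interviewee about acceptability and burden.

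The planned number of interviews and the honorarium per interview stay the same. Non-completers may be harder to schedule. A minor ethics amendment may be needed, since three boards approved the project.

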**Secondary objective (A)**				
Describe the change in provider (i) knowledge and skill accuracy to recognize and respond to IPV and child maltreatment, as well as change in their perceived; (ii) preparedness to recognize and respond to IPV and child maltreatment; (iii) attitudes towards recognizing and responding to IPV and child maltreatment from baseline to post-intervention and 3-month, follow-up timepoints	Proof of concept/educational impact	Quantitative research assessments; *provider self-report*	**Hypothesis:** Self-reported knowledge and skill accuracy (*Child Maltreatment Vignette Scale; Actual Knowledge Subscale - PREMIS*), preparedness (*Mandatory Reporting Self-Efficacy Scale; Preparedness Subscale-PREMIS measure*), attitudes (*Role Beliefs Scale*) will be better at all follow-up timepoints, relative to baseline	Regression analysis
**Secondary objective “B”**				
Describe the change in the number of referrals made by enrolled providers over the previous month to (i) intimate partner violence services; (ii) parenting services/interventions; (iii) child welfare services; or (vi) psychotherapy services at baseline, post-intervention, and 3-month follow-up timepoints	Proof of concept/educational impact	Quantitative research assessments; *provider self-report*	**Hypothesis:** Provider self-reported referrals of patients to (i) intimate partner violence services; (ii) parenting services/interventions; (iii) child welfare services; or (vi) will be higher at all follow-up timepoints, relative to baseline	Regression analysis

#### Quantitative research strand

##### Design, sampling, and recruitment

The quantitative strand will follow a non-experimental, repeated measures design [104]. HSSPs working in primary care clinics in the provinces of Ontario, Alberta, and Quebec will be recruited to undergo the VEGA intervention and complete quantitative measures of education outcomes at multiple timepoints. Measures will be administered to determine (a) the acceptability and feasibility of collecting data on proposed educational outcome measures for a definitive trial and (b) generate preliminary estimates of effect (i.e., proof-of-concept) and variability, which can inform sample size estimations for a definitive trial. To achieve our research aims, we will use a three-stage sampling strategy; two of the three stages are relevant for the quantitative strand of data collection.

Stage 1 will occur at the clinic level. Criterion and simple random sampling strategies will be used to enlist two primary care clinics in the provinces of Ontario, Quebec, and Alberta for participation [64, 65]. Given that samples of approximately 40 participants are generally sufficient for acceptability and feasibility studies [105–107], a roster of primary care clinics with a front-line complement of between 10 and 60 HSSPs who provide health and/or social services to individuals and families in each of the eligible provinces will be generated via provincial registries made publicly available on each province’s Ministry of Health website. Two clinics per province will be selected from these rosters for participation via a simple random sampling algorithm in SPSS. Directors of the selected clinics will be contacted by the research team via email and provided with a one-page overview of the project and the opportunity to meet synchronously with the research team to address study-related questions. Directors will be asked to provide consent for clinic participation, as well as the email addresses for all HSSPs within the clinic. To be eligible to participate, the Director of each of the selected clinics must (a) provide permission for the full complement of their HSSP staff to complete study-related activities and (b) have no ongoing participation in other education-related research projects. Random selection of replacement clinics will continue until we achieve our clinic sample aims.

Stage 2 sampling will occur at the individual level; full-population sampling will involve inviting all full-time and part-time HSSPs at each of the enrolled clinics to participate in the quantitative strand of our study [108]. We anticipate that this individual, convenience sampling approach will yield between 5 and 20 practitioners participating at each of the respective clinics. Eligible practitioners will be those who (a) have worked for the selected clinic for a minimum of 2 months, (b) intend on working (to the best of their knowledge) at the clinic until the end of the study, and (c) provide informed consent and are willing to complete quantitative and qualitative study procedures.

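### Clinics are replaced until two per province enrol, so the clinic enrolment percentage runs modestly high, and the 60% benchmark is reported without an interval that would show how little six clinics can support

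*Protocol article*

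**What the plan says.** The phase 3 quantitative strand (Design, sampling, and recruitment) sets out to "enlist two primary care clinics in the provinces of Ontario, Quebec, and Alberta for participation", with a random draw from provincial rosters: "Two clinics per province will be selected from these rosters for participation via a simple random sampling algorithm in SPSS". Clinics that do not join are replaced: "Random selection of replacement clinics will continue until we achieve our clinic sample aims". The article does not print the total, but two clinics in each of three provinces makes six.

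Table 3, primary objective A, defines the outcome as "Percentage of eligible clinics who are approached and enroll". The success criterion is "A 60% or greater enrollment rate of primary care clinics approached for participation" and the analysis is "Descriptive counts, percentages, and range across provinces". The Quantitative data analysis section agrees: "quantitative data for our primary objectives in phase 3 will be analyzed using descriptive statistics". It repeats the 60% threshold without splitting it by province, and says that revisions will be considered if more than one of the listed thresholds is missed.

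Intervals are named for the education outcomes only. Primary objective C asks that the team can "generate estimates of effect and variability (with 95% confidence intervals) for the secondary outcomes", and the analysis section promises 95% intervals for the secondary objectives.

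**The concern.** When recruitment stops on reaching a fixed number of acceptances, the last clinic approached in each province is always an acceptance. Dividing acceptances by approaches then overstates the underlying acceptance rate on average. The fewer acceptances required, the larger the overstatement, so a provincial figure based on two clinics suffers more than the pooled figure based on six.

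Separately, six acceptances say little about a rate. Clinic acceptance helps determine how many clinics a definitive trial would have to approach, and the article presents phase 3 as evidence on whether such a trial is tenable. As written, the exploratory education effects carry intervals, while the proportions compared with pass marks do not.

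**Working it through.** **Inputs.** From the article: two enrolled clinics per province, three provinces, replacement until filled, threshold 60%. Not given: the true acceptance rate *p*. It is assumed common to all clinics and provinces and is varied. The roster is assumed large enough to reach six. The article gives no calculation behind the 60%, so there is no figure of its own to reproduce.

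**Distribution.** With *r* acceptances required, P(N = n) = C(n-1, r-1) p^r (1-p)^(n-r) for n ≥ r. The pooled figure has r = 6 and each province has r = 2. Approaching clinics in batches no larger than the number still needed leaves this distribution unchanged; a simulation of that scheme gave the same results.

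**Bias of the plain percentage.** E[r/N] is the sum over n of (r/n) P(N = n). For r = 2 it has the closed form 2(p²/q²)[q²/p + ln p + q], with q = 1-p. At p = 0.5 this is 2 × [0.5 - 0.6931 + 0.5] = 0.614.

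| True rate | Expected 6/N | Bias (points) | Expected 2/N | Bias (points) |
|---|---|---|---|---|
| 40% | 44.1% | +4.1 | 51.9% | +11.9 |
| 50% | 54.1% | +4.1 | 61.4% | +11.4 |
| 60% | 63.8% | +3.8 | 70.1% | +10.1 |

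Over true rates from 20% to 80% the pooled bias runs from +2.4 to +4.1 points. The estimator (r-1)/(N-1), here 5/(N-1), has expectation exactly *p*.

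**What the criterion means.** 6/N ≥ 0.60 is the same as N ≤ 10. At N = 10 the plain figure is 6/10 = 60.0% and the unbiased one is 5/9 = 55.6%.

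**Precision.** The exact 95% lower limit solves P(N ≤ n) = 0.025, which is the 2.5% quantile of Beta(6, n-5). The upper limit solves P(N ≥ n) = 0.025, which is the 97.5% quantile of Beta(6, n-6).

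| N | 6/N | 5/(N-1) | Exact 95% interval |
|---|---|---|---|
| 6 | 100% | 100% | 54.1% to 100% |
| 8 | 75.0% | 71.4% | 34.9% to 96.3% |
| 10 | 60.0% | 55.6% | 26.2% to 86.3% |
| 12 | 50.0% | 45.5% | 21.1% to 76.6% |

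For N = 6 the lower limit is 0.025^(1/6) = 0.541. No possible result has a lower limit at or above 60%.

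**Chance of meeting the benchmark.** P(N ≤ 10) = P(Bin(10, p) ≥ 6), which is 16.6% at p = 0.4, 37.7% at 0.5, 63.3% at 0.6 and 85.0% at 0.7. A true 60% therefore misses about 37% of the time.

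**Provider proportions.** The article calls about 40 participants generally sufficient and expects 5 to 20 per clinic, so 6 × 5 = 30 to 6 × 20 = 120. At the 70% completion mark, Wilson 95% intervals before any allowance for clinic are about 55% to 82% for 28/40 and about 61% to 77% for 84/120.

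**The case against.** Much of the case on the other side stands.

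- **The provincial figure is not tested.** A reader might infer that a true rate of 50% would look like a pass, because the expected provincial percentage is 61%. The article applies 60% to clinics overall; provinces enter only as a descriptive range. On the pooled figure the expected value is 54%, below the threshold.
- **The pass probabilities do not measure the stopping rule.** They equal the chance of six or more acceptances if exactly ten clinics were approached. They show small numbers, not bias.
- **One threshold does not decide the outcome.** A reader might infer that a poor acceptance rate would on its own be declared feasible. The article reacts only when more than one threshold is missed, then only considers revisions, and uses qualitative data to explain the result.
- **The unbiased estimate is not more accurate.** Root mean square error is 0.157 for 5/(N-1) against 0.158 for 6/N at a true 50%, and 0.165 against 0.161 at a true 60%. Moving the criterion to N of at most 9 would cut the chance that a true 60% passes from 63% to 48%, and a true 70% from 85% to 73%.
- **Counts are already planned.** A reader given N and six can work out either estimate and the interval.
- **The article is condensed.** Descriptive statistics do not rule out intervals for proportions, and the interval method may be set out elsewhere.

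What remains is that the article itself fixes the stopping rule, the plain percentage, the threshold and the analysis for objective A. As stated, these give a figure that runs high and carries no measure of its uncertainty.

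**Conclusion.** The point holds as an inexpensive improvement, not as a flaw that invalidates the feasibility assessment. The stopping rule biases the pooled clinic percentage upward by about 4 points near 60%, and the descriptive provincial percentages by about 10 to 12 points. The greater weakness is imprecision: at the pass boundary the data are compatible with acceptance anywhere from 26% to 86%, and even a perfect result does not exclude rates below 60%.

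These figures assume a common acceptance rate, a roster that is not exhausted, replacement only up to the target, and a denominator that counts every clinic approached. If a roster ran out before the target was met, the bias would shrink. Descriptive reporting suits a feasibility aim, and the documents do not support the stronger conclusion that the 60% criterion must be tightened or abandoned.

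**What to change.** Keep 60% as a descriptive benchmark for clinic enrolment and add the following to the phase 3 analysis:

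- Report N with an exact 95% interval valid for sampling that stops at six acceptances, using the formula shown above.
- Show 5/(N-1) beside 6/N.
- Give provincial results as clinics approached and clinics enrolled, without percentages.
- Give 95% intervals that allow for clinic for provider enrolment, VEGA completion and retention.

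This takes a few lines of analysis and changes nothing in recruitment, eligibility or the intervention; the research coordinator already tracks the counts. The downside is presentational. The clinic figure looks slightly less favourable (55.6% beside 60.0% at N = 10), and the wide intervals make it plain that the benchmark cannot be decisive.

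### The provider enrolment rate in Phase 3 is circular: consent is part of eligibility, enrolment is counted among the eligible, and the success criterion implies a different denominator.

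*Protocol article*

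**What the plan says.** All the text is in the Phase 3 part of the Protocol article.

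**Providers.** Under Design, sampling, and recruitment (Stage 2), all full-time and part-time HSSPs at each enrolled clinic are invited. Eligibility has three conditions: (a) at least 2 months at the clinic, (b) intent to stay until the study ends, and "c) provide informed consent and are willing to complete quantitative and qualitative study procedures". In Table 3, primary objective B, the outcome measure is "Percentage of eligible providers that enroll" and the success criterion is "A 60% or greater enrollment rate of providers at each of the clinics". The Quantitative data analysis section restates the threshold as the proportion of "primary care clinics and their HSSPs agreeing to participate will be 60% or greater" and gives no denominator. Under Quantitative data collection, the coordinator counts HSSPs who inquire, who are eligible and who enrol. The number invited is not in that list.

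**Clinics.** In Stage 1 the director must "provide permission for the full complement of their HSSP staff to complete study-related activities" for the clinic to be eligible. In Table 3, primary objective A, the outcome measure is "Percentage of eligible clinics who are approached and enroll" and the criterion is "A 60% or greater enrollment rate of primary care clinics approached for participation". The coordinator tracks the number of clinics approached.

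**The concern.** Listing consent among the eligibility criteria is common and usually does no harm. Here the ratio of enrolled to eligible is itself a primary feasibility outcome with a pass mark. If consent is needed to be eligible, refusal cannot lower that ratio, and a clinic where most staff decline reports the same figure as one where nearly all accept.

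The 60% threshold is one of the protocol's a priori tests of whether a definitive trial is workable. Revisions to procedures are to be considered if more than one threshold is missed. A provider rate that cannot register refusal adds nothing to that rule. If two denominators remain open, the team could settle on one after seeing the enrolment data, and so choose the result.

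**Working it through.** The 60% is a set threshold, so there is no derived figure to reproduce. The check is on the denominators.

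**Inputs from the protocol**
- Clinic complement: 10 to 60 HSSPs (Stage 1).
- Anticipated participants per clinic: 5 to 20 (Stage 2).
- Clinics: 2 per province × 3 provinces = 6, with random replacement until that number is reached (Stage 1).
- Threshold: 60% for both providers and clinics (Table 3).

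**Step 1: provider rate on the stated outcome definition.** Rate = enrolled / eligible. Eligible means (a), (b) and consent with willingness. Everyone in the denominator has already agreed, so the rate is about 100% at any uptake.

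**Step 2: provider rate among those invited.** Rate = enrolled / invited, taking the number invited as the stated complement (an assumption).
- Low ends paired: 5/10 = 50%, fail; 6 of 10 are needed.
- High ends paired: 20/60 = 33%, fail; 36 of 60 are needed.
- Other pairings go further each way: 5/60 = 8%, and 20/20 = 100%.
- The anticipated maximum of 20 reaches 60% only with a complement of 33 or fewer: 20/33 = 60.6%, 20/34 = 58.8%.

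**Step 3: does removing staff who fail (a) or (b) rescue these cases?** With 5 enrolled the denominator would have to fall from 10 to 8 (5/8 = 62.5%; 5/9 = 55.6%). With 20 enrolled it would have to fall from 60 to 33, that is, 27 of 60 staff failing (a) or (b). The first is possible. The second would need nearly half the staff to be new or planning to leave.

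**Step 4: chance of passing at one clinic.** Assume 30 invited, within the stated 10 to 60, and independent decisions. Passing needs 0.6 × 30 = 18. With X ~ Binomial(30, p):

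| True uptake p | P(X ≥ 18), invited as denominator | Eligible-based rate |
|---|---|---|
| 10% | < 0.001 | about 100%, pass |
| 30% | 0.0006 | about 100%, pass |
| 50% | 0.18 | about 100%, pass |
| 60% | 0.58 | about 100%, pass |

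The invited-based rate separates poor uptake from good. The eligible-based rate does not.

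**Step 5: clinics.** Rate on the stated criterion = enrolled / approached. With 6 enrolled, 6/10 = 60% passes and 6/11 = 54.5% fails. The criterion can therefore fail. The inconsistency is confined to the outcome cell, which refers to eligible clinics: with director permission as an eligibility condition, a refusing clinic could be classed as ineligible there.

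**The case against.** The strongest reply is that the authors plainly meant something sensible. The provider criterion speaks of providers at each clinic, without the word eligible. The analysis section speaks of HSSPs agreeing to participate, which makes sense only if those who do not agree are counted. The coordinator logs eligible and enrolled as separate numbers. Everyone is invited, and directors supply e-mail addresses for all HSSPs, so the number invited is obtainable. The proceed rule asks only that revisions be considered, puts clinic and provider agreement in one item, and is supported by other thresholds and by interviews.

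Much of this stands. A non-circular reading of the provider criterion is available, and provider enrolment alone does not settle whether a trial goes ahead. Because the article condenses a fuller protocol, the absence of an invited count from the tracking list would not be a fault taken alone. But the non-circular reading leaves the outcome column and the criterion column of one row in disagreement, and the stated eligibility definition sides with the circular one. That is a conflict in what is written, not a matter of omitted detail.

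A reader might also infer that the clinic threshold is met by definition, since eligibility needs director permission and the outcome cell refers to eligible clinics. The documents do not support that. The criterion, the objective and the tracking list all use clinics approached, so a refusing clinic stays in the denominator.

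**Conclusion.** The point holds for providers. The outcome for primary objective B is circular as defined and conflicts with its own success criterion. On the outcome definition the rate is about 100% at any uptake; among invited staff the paired ends of the protocol's ranges give 50% and 33%, both below 60%. Those two figures are illustrations. They assume that the number invited equals the stated complement and that low yield goes with small clinics and high yield with large ones. Other combinations would pass, such as 20 of 30 (67%). The circularity depends on none of these assumptions.

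It would go too far to say that the provider threshold cannot fail on any reading, because the criterion's own wording allows a denominator of all providers. For clinics, only the wording of the outcome cell needs correction.

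**What to change.** - Take consent and willingness out of the eligibility definition used for the denominator, and keep them as conditions of enrolment. Do the same with director permission for clinics.
- Define the provider rate as enrolled HSSPs divided by all invited HSSPs at the clinic, excluding only those known to fail condition (a) or (b).
- Define the clinic rate as clinics enrolled divided by all clinics approached, including replacements.
- Use the same wording in Table 3 (primary objectives A and B), in Design, sampling, and recruitment, and in Quantitative data analysis.
- Add the number invited, available from the directors' e-mail lists, to the coordinator's tracking list.
- Settle this before any enrolment data are seen.

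The cost is a change of wording and one extra tracked count. The reported provider rate will be less favourable, and the 60% threshold may be missed at clinics where the eligible-based rate would have passed.
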